### Anti-osteoporotic treatment

Zoledronic acid is an anti-osteoporosis agent that rapidly and markedly increases the BMD of vertebral bone. Injections of zoledronic acid (Aclasta, Novartis Pharma Schweiz AG) will be recommended for patients who do not have contraindications for receiving zoledronic acid. If the patients agree to receive zoledronic acid treatment, 5 mg of Aclasta (Novartis Pharma Schweiz AG) will be administered 3 days after PKP, and Vitamin D and calcium supplements will also be continued.

### PKP features

Bipedicular kyphoplasty will be performed in this study. The balloon volume (BV), cement volume (CV), recovery of vertebral height, and bone cement leakage will be evaluated as factors that influence the risk of vertebral refracture. 1) The balloon volume will be recorded by the surgeons during the operation. 2) The cement volume will be recorded by the surgeons during the operation. 3) The anterior height of the fractured vertebra will be immediately measured with the picture archiving and communication systems (PACS) imaging display software (Zhejiang Public Information Industry Co., China) when the patients are enrolled and at 12 m and 24 m after PKP. Recovery of vertebral height will be defined as the anterior height of the fractured vertebra/the average height of the two adjacent vertebrae. 4) Bone cement leakage will be evaluated using radiographic evaluation during operation.

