## Abstract

**Background:**

Percutaneous kyphoplasty (PKP) is the first-line treatment for osteoporotic vertebral compression fractures (OVCFs) that can immediately relieve pain and allow the quick recovery of lost mobility. However, some studies reported that after PKP, the incidence of vertebral refracture, particularly adjacent vertebral fracture (AVF), was high. Our previous meta-analysis suggested that the risks for vertebral refracture and AVF did not increase after percutaneous vertebral augmentation in OVCF patients. Despite the negative results of our meta-analysis, there is still significant evidence regarding the relationship between kyphoplasty and AVF, so a new prospective cohort study is warranted. In addition, in our previous retrospective study, we found that advanced age, female sex and low oestradiol (E_2_) concentrations might be related to the occurrence of postoperative vertebral refracture after PKP. To sufficiently evaluate the probable factors involved in the occurrence of postoperative vertebral refracture, we designed this prospective study.

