**Methods:**

This is a prospective cohort study of patients admitted for PKP to treat painful OVCFs. The baseline data, including demographic information, lifestyle, bone metabolic status, sex hormone and sex hormone-binding globulin (SHBG) levels, and clinical characteristics will be collected at the time of enrolment. Surgical features of PKP will be recorded on the operation day. Lifestyle, bone metabolic status, sex hormone levels, and SHBG levels will be assessed during the follow-up period at 1 m, 3 m, 12 m, and 24 m postoperatively. Patients suffering from acutely aggravated back pain will be referred to an orthopaedist, and refractured vertebrae will be confirmed by magnetic resonance imaging and computed tomography. The primary outcome will be the incidence of vertebral refracture. Multivariate analyses will be carried out to evaluate the variables that are independently correlated with vertebral refracture.

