### Anthropometric data

The baseline data, including gender, age, weight, height, and BMI will be collected following participant recruitment (Table 1). Body weight and height will be measured twice with a height and weight scale (HW-900B, Kaiyuan Electronic Co., Zhengzhou, China) while the patients are wearing light clothes and are barefoot, and then the mean reading will be recorded. Body mass index (BMI) will be calculated as the body weight in kilograms divided by the square of the body height in metres.

**Table 1 Tab1:** Timeline of data collection

Data collection		Pre	Op	1 m	3 m	12 m	24 m	OR
Demographic information	Gender	√						
	Age	√						
	Height	√						
	Weight	√						
	BMI	√						
Life style	Tobacco consumption	√		√	√	√	√	√
Bone metabolic status	BMD	√		√	√	√	√	√
	Bone metabolic markers	√		√	√	√	√	√
	Anti-osteoporosis treatment	√		√	√	√	√	√
Sex hormone	Serum hormone concentrations	√		√	√	√	√	√
	SHBG	√		√	√	√	√	√
Clinical characteristics	Affected vertebra number	√						
	VAS score	√		√	√	√	√	√
Surgical features	Balloon volume		√					
	Cement volume		√					
	Vertebral height	√	√			√	√	√
	Bone cement leakage		√					

Pre: pre-operation. Op: operation. 1 m, 3 m, 12 m, 24 m: one month, three months, 12 months, 24 months postoperatively. *OR* Orthopedist review

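### Recovery of vertebral height is defined as a static height ratio with no before-and-after comparison, and the text omits the operation-day reading that Table 1 schedules

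*Protocol article*

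**What the plan says.** The PKP features section of the protocol article lists balloon volume and cement volume and continues that "recovery of vertebral height, and bone cement leakage will be evaluated as factors that influence the risk of vertebral refracture". It gives an explicit formula for the third of these four factors: "Recovery of vertebral height will be defined as the anterior height of the fractured vertebra/the average height of the two adjacent vertebrae".

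On timing, that section has the anterior height measured "when the patients are enrolled and at 12 m and 24 m after PKP". Table 1 (under Anthropometric data) has a row "Vertebral height" within the surgical features. It is ticked at Pre, Op, 12 m, 24 m and OR (orthopaedist review), and the footnote reads "Pre: pre-operation. Op: operation". The Methods paragraph of the abstract adds: "Surgical features of PKP will be recorded on the operation day".

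On the outcome, the abstract states: "The primary outcome will be the incidence of vertebral refracture". Its background explains the motivation by reports that after PKP "the incidence of vertebral refracture, particularly adjacent vertebral fracture (AVF), was high". The Analysis section plans univariate and multivariate logistic regression for refracture. It does not say which height reading enters the models.

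**The concern.** Recovery means a change from before to after the procedure, and the formula contains no earlier value. Applied as written, it measures how deformed the treated vertebra is at the time of the image, and the result would be reported under the name of height recovery. The study wants to identify points of surgical technique that bear on refracture, and for that purpose residual deformity and height gained are different exposures.

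Two features add to this. First, the section that defines the variable omits the reading closest to the procedure, which Table 1 includes. Second, the denominator consists of the neighbouring vertebrae, whose fracture is part of the outcome and the type of refracture of most interest. A reading taken after such a fracture is partly a consequence of the outcome and cannot serve cleanly as its predictor.

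**Working it through.** The plan gives no figure for this variable, so there is none to reproduce. The heights below are assumptions that show how the formula behaves. An intact neighbour is set to 1, both neighbours are equally tall, and all heights are taken in the same dimension.

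**1. Does the formula express recovery?** The protocol's ratio is R = h(treated) / mean(h(above), h(below)).

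| Patient | R before | R after | Protocol score after PKP | Change in R |
|---|---|---|---|---|
| A | 0.50 | 0.80 | 0.80 | 0.80 - 0.50 = 0.30 |
| B | 0.80 | 0.80 | 0.80 | 0.80 - 0.80 = 0 |

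The protocol's score does not separate A from B. The change in R does.

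**2. Which readings exist?**

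| Time | PKP features text | Table 1 |
|---|---|---|
| Before operation | yes (enrolment) | yes |
| Operation | no | yes |
| 1 m, 3 m | no | no |
| 12 m, 24 m | yes | yes |
| Orthopaedist review | no | yes |

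The text has two postoperative readings, at 12 m and 24 m. It lacks the operation-day and review readings.

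**3. What does an adjacent fracture do to a later reading?** If one neighbour loses a fraction L of its height, the denominator becomes (1 + 1 - L)/2 = 1 - L/2, so R is multiplied by 1/(1 - L/2). With the treated vertebra fixed at 0.80:

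| L | Factor | R |
|---|---|---|
| 0.10 | 1/0.95 = 1.053 | 0.84 |
| 0.20 | 1/0.90 = 1.111 | 0.89 |
| 0.25 | 1/0.875 = 1.143 | 0.91 |
| 0.40 | 1/0.80 = 1.25 | 1.00 |

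This applies to a reading taken after the fracture. An operation-day reading cannot be altered by a later fracture.

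**4. Is the direction fixed?** If the treated vertebra also loses a fraction K, the factor is (1 - K)/(1 - L/2). It exceeds 1 when K < L/2, equals 1 when K = L/2 (for example L = 0.25 and K = 0.125), and is below 1 when K > L/2. A remote refracture has L = 0 and, with K = 0, leaves R unchanged. The net direction over all refractures therefore cannot be settled from the documents.

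**5. Are the neighbours sound at baseline?** The exclusion criteria remove previous vertebral fracture, not several acute fractures, and the number of affected vertebrae is recorded. If a neighbour is already fractured with L = 0.25, patient A's ratios become 0.50/0.875 = 0.571 and 0.80/0.875 = 0.914. Their difference is 0.343 instead of 0.30. A change score therefore also needs unfractured reference vertebrae.

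**The case against.** The strongest reply is that the plan already points to the operation. Table 1 files vertebral height under surgical features with ticks at Pre and Op, the abstract places surgical features on the operation day, and the Data collection section has them recorded during PKP. On that reading the time list in PKP features is merely incomplete. The operation-day value is the natural predictor, a later adjacent fracture cannot touch it, and a change can be derived from data already scheduled. Which repeated reading enters a model is also a detail that an article may leave to the analysis plan.

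Much of this stands. A reader might infer from the text that height is never measured after the procedure. That is not so: 12 m and 24 m are postoperative, and Table 1 supplies the operation-day reading. Nor do the documents say that a late reading will be the predictor, so the distortion by adjacent fracture is conditional. A reader might go further and expect better restoration to appear to cause refracture. The documents do not support that either, because the outcome includes remote fractures and the treated vertebra can itself lose height.

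The reply does not rescue the formula. Even on the operation day the stated ratio has no preoperative term and scores patients A and B alike. That is a stated rule that does not fit its label, and not a detail left for later. The word immediately in the measurement sentence does not help, since the dates attached to it include no operation-day reading.

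**Conclusion.** The point holds in this form. The variable called recovery is a static relative height without a pre-to-post comparison, and the text omits the operation-day and review readings that Table 1 ticks. The first defect follows from the formula alone and needs no assumption about heights.

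The link to the outcome through the denominator holds only if a reading after an adjacent fracture is used as the predictor. Its size then depends on L: for one fractured neighbour of equal height, R rises by 11% at L = 0.20 and by 25% at L = 0.40, before any change in the treated vertebra. These are properties of the ratio under assumed heights, not estimates of bias in this study, and the net direction is undetermined.

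The severity is should-fix. The affected variable is one candidate predictor among many. The outcome is untouched, and so is the sample size, which rests on age and E2. The data for a correct measure are scheduled in Table 1, so nothing is lost if the definition is changed.

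**What to change.** 1. In PKP features, define recovery of vertebral height as the operation-day ratio minus the preoperative ratio. Normalise each ratio within its own image to the nearest unfractured vertebrae above and below, using the same reference levels in both images. A difference of ratios is preferable to a difference of raw heights, because it keeps the within-image scaling and does not count a difference in magnification as recovery.
2. State that this change is the value entering the univariate and multivariate regressions.
3. Align the measurement times in PKP features with Table 1, so that the operation-day and orthopaedist-review readings appear in both.
4. State that 12 m, 24 m and review heights describe later height loss and are not used as predictors of refracture.

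The cost is wording only. Table 1 already schedules the preoperative and operation-day readings, and no visit is added. Where neighbouring levels are fractured together at baseline, the reference heights come from the next unfractured level.

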### Analysis

Quantitative variables will be summarized by the mean ± SD, and qualitative variables will be presented as counts and percentages. Continuous parameters of patients with and without vertebral refracture will be compared by analysis of variance (ANOVA), and binary parameters will be evaluated with logistic regression. A Pearson regression model will be used to analyse the correlation between the incidence of vertebral refracture and the covariates. Univariate and multivariate logistic regression analyses will be carried out to identify the independent predictors of vertebral refracture. A value of *P* < 0.05 will be considered statistically significant. Statistical analyses will be carried out using the SPSS 19.0 statistics package (SPSS, Chicago, IL, USA).

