### Sample size

The sample size calculation was performed using Epi Info 7.2 software (www.cdc.gov/epiinfo/index.html) for the following risk factors: age and E_2_ level. Based on our previous retrospective study, the ratio of patients < 80 years old and those ≥ 80 years old is nearly 5:1, and the ratio of patients with E_2_ levels ≥ 50 pmol/L and those < 50 pmol/L is nearly 3:1 [24]. A two-sided test will be set with an α risk of 0.05 and a power of 80%. Our previous retrospective study showed that the incidence of refracture was nearly 9% in the patients < 80 years old, 33% in patients ≥ 80 years old, 2% in patients with E_2_ levels ≥ 50 pmol/L, and 40% in patients with E_2_ levels < 50 pmol/L. The calculated required sample size for the cohort is 164 patients to evaluate the risk factor of age and 50 patients to evaluate the risk factor of E_2_ levels. Therefore, assuming a rate of loss to follow-up of 10%, 180 participants will be included.

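### About 19 to 21 expected refractures are too few to support a search for independent predictors among 17 to 22 recorded factors

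*Protocol article*

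**What the plan says.** The Analysis section of the protocol article states: "Univariate and multivariate logistic regression analyses will be carried out to identify the independent predictors of vertebral refracture". The threshold there is a P value below 0.05, with no distinction between factors: "0.05 will be considered statistically significant". The Methods part of the Abstract makes this the headline analysis: "Multivariate analyses will be carried out to evaluate the variables that are independently correlated with vertebral refracture".

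The Primary objectives section names general characteristics, bone status, anti-osteoporotic treatment, sex hormones with SHBG, and the procedure itself as the domains to be studied. The Methods subsections and Table 1 list the variables within them.

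The Sample size section considers only age and E2, each as a two-group comparison: "A two-sided test will be set with an α risk of 0.05 and a power of 80"%. For age it assumes that "the ratio of patients < 80 years old and those ≥ 80 years old is nearly 5:1" and that "the incidence of refracture was nearly 9% in the patients < 80 years old, 33% in patients ≥ 80 years old". For E2 it assumes a 3:1 split at 50 pmol/L, with a refracture rate of 2% above the cut "and 40% in patients with E_2_ levels < 50 pmol/L". This gives 164 and 50 patients, and 180 are to be enrolled to allow for 10% loss to follow-up.

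**The concern.** The information in a logistic model is limited by the number of events, not the number of patients. Taken together, the article's own rates, cohort size, factor list and significance rule leave about one refracture for each factor that may be declared an independent predictor. With so few events, maximum-likelihood odds ratios tend to lie too far from 1, and tests at a nominal 5% reject somewhat too often. Testing many factors at 5% each also makes some false finding likely.

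This matters because naming predictors is the primary objective. The second stated objective is to use them to define which patients are suitable for the procedure. A false or exaggerated predictor would feed directly into that.

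**Working it through.** **1. The plan's own sample size.** The inputs are those of the Sample size section. The two-proportion formula with continuity correction (Fleiss), with n1 patients in the larger group, r = n2/n1 and p̄ = (p1 + r·p2)/(1 + r), is:

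- n = [1.96·√((r+1)·p̄(1−p̄)) + 0.84·√(r·p1(1−p1) + p2(1−p2))]² / [r·(p1−p2)²]
- corrected n1 = (n/4)·[1 + √(1 + 2(r+1)/(n·r·|p1−p2|))]²

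Age (0.09 vs 0.33, r = 1/5): 136 + 28 = 164. E2 (0.02 vs 0.40, r = 1/3): 37 + 13 = 50. Both match the stated figures. The sizing of the two single-factor comparisons is therefore not the fault.

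**2. Expected refractures.**
- Overall risk from the age rates: (5 × 0.09 + 0.33)/6 = 13.0%
- Overall risk from the E2 rates: (3 × 0.02 + 0.40)/4 = 11.5%
- Evaluable patients: 180 × 0.90 = 162
- Expected events: 162 × 0.130 = 21.1 and 162 × 0.115 = 18.6
- With no loss at all: 180 × 0.130 = 23.4 at most

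**3. Candidate factors.** The Methods subsections describe:

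| Domain | Variables |
|---|---|
| Gender, age, height, weight, BMI | 5 |
| Smoking (four classes, 3 df) | 1 |
| BMD at spine and hip | 2 |
| BAP, NTX | 2 |
| Anti-osteoporotic treatment | 1 |
| FSH, LH, testosterone, E2, SHBG | 5 |
| Number of affected vertebrae | 1 |
| VAS | 1 |
| Balloon volume, cement volume, height recovery, leakage | 4 |
| Total | 22 (24 df) |

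A stricter count drops height and weight (inputs to BMI), one BMD site, VAS and the number of vertebrae: 22 − 5 = 17. Table 1 also has 17 rows. Repeat measurements during follow-up are not counted.

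**4. Events per candidate.**
- 22 candidates: 18.6/22 = 0.85 to 21.1/22 = 0.96
- 17 candidates: 18.6/17 = 1.1 to 21.1/17 = 1.2
- 17 candidates with complete follow-up: 23.4/17 = 1.4

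**5. Consequence, by simulation.** The assumptions are N = 162, one sixth aged 80 or over, refracture 33% vs 9%, mutually independent covariates and maximum-likelihood logistic regression at P < 0.05. The true age odds ratio is (0.33/0.67)/(0.09/0.91) = 4.98.

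| Setting | At least one false predictor | Other results |
|---|---|---|
| Age real, univariate screening at 0.05, then multivariable model | about 43-52% | |
| Age and E2 real, 20 null factors, same screening | about 34-35% | |
| Age real, 21 null factors, all entered | about 74% | median age OR about 8.4; per-test error about 7.3% |

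Twenty-one independent, correctly calibrated 5% tests would already give 1 − 0.95²¹ = 66%. Multiplicity thus accounts for most of the 74%, and overfitting adds about 74 − 66 = 8 points. The shift of the odds ratio from 5.0 to 8.4 is the effect of overfitting proper. With only four extra covariates, the median age odds ratio stays close to its true value and the per-test error is about 5%. The trouble therefore comes from the ratio of factors to events.

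**The case against.** The strongest reply is that the article never says all 22 factors enter one model. Its wording is compatible with univariate screening, and entry rules or shrinkage are often left to a fuller plan that is not shown here. The count of 22 is an upper figure, since Table 1 is a data-collection timeline and not a list of model terms. Much of the simulated false-positive rate is ordinary multiplicity, in a study whose objective is worded as exploration. The simulations treat almost every other factor as null and independent, although the Background cites evidence for several of them.

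These points stand as limits on size. They do not remove the mismatch. Seventeen candidates still leave little more than one event each. Screening shrinks the fitted model but not the number of factors tested, and a false predictor still appears in a third to a half of simulated studies. The article also goes beyond exploration by undertaking to identify independent predictors at P < 0.05.

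A reader might infer more than the documents support:

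- **The E2 odds ratio may not be estimable.** About 162 × 3/4 ≈ 122 patients would have E2 at or above 50 pmol/L. The chance of no event among them is 0.98¹²² = 8.5%, and this matters only if E2 is dichotomised at that value in the model. The article uses the cut for sample size and does not say that it will be used in the analysis.
- **The sample size calculation is wrong.** The figures 164 and 50 reproduce exactly.
- **The predictors found are bound to be partly spurious.** This is likely, not certain.

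**Conclusion.** The point holds as a mismatch between the stated analysis and the information the cohort will supply: about 19 to 21 events for about 17 to 22 candidates, or roughly 0.9 to 1.2 events each. The multivariable model is likely to be overfitted. If it is built by univariate screening, the chance of at least one false independent predictor is about 43-52% when age alone is real, and about one third when E2 is real as well. The 74% figure and the age odds ratio of about 8.4 apply only if all 22 factors are entered together, which the article does not state.

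The event count rests on the article's own rates and its 10% loss assumption. The percentages rest on the simulation assumptions of independent covariates and no effect of the remaining factors. They would change if the covariates were correlated or if more of them had real effects. The two single-factor comparisons on which the cohort was sized are not affected.

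**What to change.** Amend the Analysis section before any modelling:

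- Pre-specify one small primary multivariable model of about 4-5 df that includes age and E2, the two factors the study is sized for. The investigators choose the remaining terms in advance and state whether E2 is continuous or categorised.
- Fit it by penalised likelihood (for example Firth), with no selection on univariate P values. Even 4-5 df leaves only 18.6/5 = 3.7 to 21.1/4 = 5.3 events per parameter, so the penalty is still needed.
- Use BMI in place of height, weight and BMI together, because BMI is computed from the other two.
- Report all other factors as exploratory estimates with confidence intervals, and do not call them independent predictors. A false-discovery-rate adjustment is optional.

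The choice of Firth or ridge and the exact additional covariates are matters of preference. The change needs no extra patients or data. Its costs are a protocol amendment with ethics approval, software that offers penalised likelihood, and fewer factors that can be called independent predictors.

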### Amendment of the protocol

A formal amendment to the protocol will be required before any modifications to the protocol are made. Any amendments will be approved by the Ethics Committee of the First Affiliated Hospital of Zhejiang Chinese Medicine University before implementation.

